### Outcomes

Outcomes at baseline and follow-up were assessed in four domains:

1. Puberty and growth
2. Medical safety
3. Bone health
4. Psychological function

Two outcomes were assessed only during or after treatment.

1. Treatment satisfaction
2. Decision made at the end of treatment.

The Table below lists the specific outcomes from each domain, along with their expected or hypothesised change from baseline and the analytic plan for each outcome.

| **Outcome** | **Description and measurement** | **Timing** | **Expected or hypothesised change on GnRHa** | **How assessed for study outcomes** |
| --- | --- | --- | --- | --- |
| A. PUBERTY & GROWTH | |  |  |  |
| 1. Gonadotropins and sex steroids | Gonadotropins (LH, FSH; in both sexes), testosterone (in birth-registered males) and oestrogen (birth-registered females) | At 6 and 12 months then annually | The aim of GnRHa treatment was to suppress LH and FSH production, leading to the ‘turning off’ of gonads and therefore suppression of testosterone or oestrogen (depending on birth registered sex).  Hypothesis: that hormones will be suppressed to prepubertal levels by 6 to 12 months. | a. Categorical: Report of whether sex steroids and gonadotropins were suppressed at 6 to 12 months  b. Mean value and 95% CI for hormones at 12, 24 and 36 months |
| 2. Growth | Height, weight and calculated BMI | 6 monthly initially and thereafter 12-monthly | Height: Height growth during puberty is dependent on the twin effects of sex steroids (oestrogen or testosterone) and growth hormone. The pubertal growth spurt occurs around Tanner stage 2-3 in females and stage 3-4 in males. GnRHa treatment is expected to dramatically reduce height growth compared to adolescent peers who are growing rapidly. This will show as only small growth in height but a fall in height z-score (i.e. standard deviation score adjusted for age and sex).  Hypothesis: height velocity will be reduced to prepubertal levels, with a matching fall in height z-score.  Weight and BMI: No definitive hypotheses. We will examine weight and BMI standardized for age and sex through use of weight and BMI z-score. | z-scores for height, weight and BMI calculated for age and sex at 12, 24 and 36 months using the UK 1990 growth reference.  Analysis will be restricted to calculation of means and 95% confidence intervals (95% CI) at each time point, and no statistical testing will be done |

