| 1. Bone mineral density | DEXA scan report of bone mineral density in lumbar spine (L1-4) and hip:  Primary outcomes in spine and hip:  1. Bone mineral content (BMC)  2. Bone mineral density (BMD)  Secondary outcomes: calculated BMD z-score for age & sex, regression-adjusted for change in height z-score (height adjusted z-score: HAZ) | Annually | There is a strong relationship between bone strength, height and puberty. Normatively, BMC and BMD rise during adolescence due to the action of sex steroids on bone mineral accretion and because of height growth.  This will not occur if puberty is suppressed, as height does not increase and because bone mineral accretion is not promoted by sex steroid. The expectation is therefore that during GnRHa treatment bone strength as measured by BMC and BMD will not fall during treatment – but that it will not increase as expected from age and height growth. BMD z-scores for age reflect population increases in bone mineral, therefore z-scores will fall if puberty is suppressed, although without any reduction in bone strength.  We hypothesise that there will be no change in absolute BMD nor in BMC. However we expect that BMD z-score will fall consistent with falls in height z-score i.e. that HAZ will remain constant. | Change in continuous measures of BMC, BMD and BMD HAZ at 12, 24 and 36 months.  Formal statistical testing will be restricted to change in BMC and BMD as primary outcomes. Means and 95% confidence intervals (95% CI) will be calculated for HAZ at each time point. |
| D. PSYCHOLOGICAL FUNCTION |  |  |  |  |

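### The no-change benchmark for the tested bone outcomes assumes no height growth, which the plan's growth row contradicts, and stable areal BMD in a growing skeleton can hide lower size-corrected density

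*SAP*

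**What the plan says.** All of this is in the SAP, Outcomes table.

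- **C.1 Bone mineral density, premise.** The row gives two causes for the normal adolescent rise in BMC and BMD: sex steroids and height growth. It then rules out both under suppression: "This will not occur if puberty is suppressed, as height does not increase and because bone mineral accretion is not promoted by sex steroid".
- **C.1, hypothesis.** "We hypothesise that there will be no change in absolute BMD nor in BMC". The row treats BMC and BMD as measures of bone strength, and says of the age-standardised scores: "therefore z-scores will fall if puberty is suppressed, although without any reduction in bone strength".
- **C.1, testing.** "Formal statistical testing will be restricted to change in BMC and BMD as primary outcomes". Both are measured at lumbar spine and hip. Analysis methods specifies paired t-tests.
- **C.1, secondary outcome.** The BMD z-score is "regression-adjusted for change in height z-score (height adjusted z-score: HAZ"). It is expected to stay constant and is reported without a test: "Means and 95% confidence intervals (95% CI) will be calculated for HAZ at each time point".
- **A.2 Growth.** Height growth is expected to slow, not stop: "This will show as only small growth in height but a fall in height z-score". The hypothesis is that "height velocity will be reduced to prepubertal levels, with a matching fall in height z-score".

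**The concern.** The bone row needs height to stand still, while the growth row expects it to rise slowly. Prepubertal velocity is reduced but positive growth. The bone row itself names height growth as a reason why BMC and BMD rise, so by its own reasoning a cohort that is still growing should show some rise if density is preserved. Zero change is then the wrong benchmark for preserved density.

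BMC and BMD are the only bone outcomes formally tested, and neither is corrected for bone size. Analysis methods describes the sample as small, and the SAP states no margin for the paired t-tests, so a non-significant change is easy to obtain. That result would match the hypothesis that the plan links to no loss of strength. Any error therefore runs towards reassurance on a safety outcome.

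**Working it through.** The SAP gives no baseline height, velocity, margin or sample size for bone, so there is no stated figure to reproduce. The check is one of internal consistency, followed by an illustration under stated assumptions.

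**Inputs from the SAP:** height growth small but positive (A.2); BMC and BMD hypothesised unchanged (C.1); results at 12, 24 and 36 months (C.1 and Analysis methods).

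**Assumptions not in the SAP:** DEXA BMD is areal, i.e. BMC divided by projected area; baseline height 155 cm; velocity 2 to 5 cm/year; the scanned region grows in proportion to height.

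**Formulas.** Let L = follow-up height / baseline height. Area scales as L² and volume as L³.

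1. BMD = BMC / area, so area = BMC / BMD. If L > 1, area rises and BMC and BMD cannot both be constant.
2. Constant volumetric density: BMC changes by L³ − 1 and areal BMD by L − 1. Both should rise.
3. Constant areal BMD: BMC changes by L² − 1 and volumetric density by 1/L − 1.
4. Constant BMC: areal BMD changes by L⁻² − 1.

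**Length ratios.** 12 months: 157/155 = 1.0129 to 160/155 = 1.0323. 24 months: 159/155 = 1.0258 to 165/155 = 1.0645. 36 months: 161/155 = 1.0387 to 170/155 = 1.0968.

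| Month | Constant areal BMD: BMC | Constant areal BMD: volumetric density | Constant BMC: areal BMD |
|---|---|---|---|
| 12 | +2.6% to +6.6% | −1.3% to −3.1% | −2.5% to −6.2% |
| 24 | +5.2% to +13.3% | −2.5% to −6.1% | −5.0% to −11.8% |
| 36 | +7.9% to +20.3% | −3.7% to −8.8% | −7.3% to −16.9% |

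At 1 cm/year, L = 156/155 = 1.0065 at 12 months, and constant areal BMD implies volumetric density 0.6% lower.

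**Reading the table.** In the constant-BMC case the loss appears as a fall in areal BMD, which is itself a tested primary outcome. In the constant-areal-BMD case one tested outcome is flat and the other rises, so neither signals a loss although volumetric density has fallen. This second case is the one the tests can miss.

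**Does BMAD detect it?** BMAD = BMC / area^1.5. Substituting area = BMC / BMD gives BMAD = BMD^1.5 / BMC^0.5. With BMD constant and BMC multiplied by L², BMAD is multiplied by 1/L, which is the volumetric fall in the table.

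**The case against.** **Unchanged BMC and BMD together do not prove a loss.** A reader might infer that they do. If both are exactly unchanged, area is unchanged, and BMAD = BMD^1.5 / BMC^0.5 is unchanged too. What stands is narrower: that joint result cannot occur in a growing bone, and two non-significant tests are compatible with a fall in size-corrected density.

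**Larger losses are not hidden.** Taking BMC alone as unchanged gives volumetric falls (1/L³ − 1) of about 4% to 9% at 12 months and 11% to 24% at 36 months. Areal BMD, the other primary outcome, would then fall by 2.5% to 6.2% and 7.3% to 16.9%, so the direction of loss would be visible.

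**HAZ is planned.** It carries 95% CIs at every time point and would tend to fall if BMD lagged behind height. This is a real but partial safeguard. HAZ is secondary, untested and for BMD only, and it adjusts for height z-score, not bone size. Height z-score is expected to fall while absolute height rises, so HAZ attributes part of a fall in BMD z-score to relative shortness. It does not show whether mineral kept pace with a larger bone. Nor does the SAP say that the primary results must be read with it.

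**There is no explicit decision rule.** The SAP nowhere says that a null test will be reported as preserved bone. That is correct, although its wording on strength invites that reading.

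**The growth may be small.** The plan says so, baseline Tanner stages run from 2 to 5, and participants near final height would show little effect. The upper end of the assumed velocities may not apply to many of them.

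**Conclusion.** The concern holds in a limited form. The bone and growth rows contradict each other on height, and the contradiction weakens the no-change benchmark for the only tested bone outcomes. The masking route is stable areal BMD with rising BMC. Its size is about 1.3% to 3.1% lower volumetric density at 12 months and 3.7% to 8.8% at 36 months, if baseline height is 155 cm, velocity is 2 to 5 cm/year and growth of the scanned region is proportional. It is below 1% per year at 1 cm/year or near final height. The SAP supplies none of these inputs, so the figures show the possible scale and do not estimate what happened in this cohort.

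The documents do not support saying that bone loss would necessarily be reported as preserved bone, or that the plan has no height-adjusted bone measure.

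**What to change.** In the SAP, Outcomes table:

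1. Reconcile the growth and bone rows on whether height increases during treatment.
2. Delete the inference that unchanged BMC or BMD means no loss of bone strength.
3. Add lumbar spine BMAD (BMC / area^1.5, with area = BMC / BMD), and report its paired change from baseline with 95% CI at 12, 24 and 36 months.
4. State that the primary BMC and BMD results at spine and hip are interpreted together with HAZ, BMAD (spine only) and absolute change in height. The growth row currently plans height z-scores, so absolute height change has to be added to the report.

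**Cost:** SAP wording and one variable derived from spine values already collected, with no new scans. The downside is one more bone measure to report. It covers the spine only, so the hip results still rely on HAZ and height change for context.

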| 1. Child Behavior Checklist (CBCL) and Youth Self-Report (YSR) | The Child Behavior Checklist (CBCL) (parent report) and Youth Self Report (YSR) (self-report) are measures of psychological functioning (aseba.org). Both provide continuous data/ t-scores for the total problem scale (a global index of functioning across all subscales). They also provide continuous data/ t-scores on the internalizing subscale (items which assess anxious/depressed, withdrawn-depressed, and somatic complaints) and the externalizing subscale (focusing on rule-breaking and aggressive behaviours). The CBCL is used for children aged 6 to 18 and consists of 113 questions. Both are scored on a three-point Likert scale (0=absent, 1= occurs sometimes, 2=occurs often). The time frame for item responses is the past six months.  Raw scores are converted for analysis to t-scores based upon broad age-ranges.  Higher scores indicate greater morbidity. | At baseline and again after around 12 months on treatment. | Normative data show an increase in CBCL internalizing scores (i.e. psychological distress) with age in early adolescence.[22] It is therefore likely that any improvements in psychological function with treatment are likely to result in smaller rises in distress with age, meaning that there will be no discernible change in psychological function over time in our cohort.  Previous data from the London service and internationally show high rates of psychological distress in young people with GID.[42] Thus our sample is a group in whom distress begins at levels higher than the general population, but who will also suffer from the normative increase in distress across the study period.  We therefore hypothesise there will be   1. no change in total problem t-scores 2. no change in externalizing or internalizing subscale t-scores   This is consistent with a potential reduction in distress due to treatment at a time when there is a developmental rise in distress. | We will use t- scores for comparison with normative published data:   1. total problems score 2. internalising subscale score 3. externalising subscale score   Change in total problems score will be tested. Change in internalising and externalising t-scores will be estimated by calculating mean and 95% CI. |

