| 2. Youth Self-Report (YSR) | The YSR is the self-report version of the CBCL (see above). The YSR is suitable for children and adolescents aged 11-18 years and consists of 112 questions.  Higher scores indicate greater morbidity.  As per the CBCL, raw scores are converted to t-scores for analysis. However t-scores are based upon broad age-ranges. To account for normative change across our age-range, we will also use international reference data[23] to transform raw scores into z-scores for age and sex. | Baseline and follow-up | Normative data show rising YSR total problems scores with age from age 11 to 16 years in healthy young people from a range of different countries.[23]  As above we hypothesize that there will be   1. no change in total problem t-scores 2. no change in z-scores for total problems 3. no change in externalizing or internalizing subscale scores | Change in total problems t-score will be tested. Change in internalising and externalising t-scores will be estimated by calculating mean and 95% CI at each time point. Change in total problems z-scores will be estimated by calculating mean and 95% CI at each time point. |

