| 3. Self-harm | This will be assessed by 2 questions in each of the CBCL (parent report) and YSR (self-report).  Item 18: I deliberately try to hurt or kill myself (self-harm)  Item 91. I think about killing myself (suicidal ideation)  For each question in both CBCL and YSR the responses are:  0=not true  1=somewhat or sometimes true  2= very true or often true  We will use these items to calculate a self-harm/suicide items score at each timepoint by sum of the 2 items in each of the CBCL and YSR, as published by other authors.[24, 25] This produces a scale from 0 to 4 for each question – with higher score indicating greater suicidality/self-harm thoughts and behaviour. |  | Self-harm rates in the general population in the UK and elsewhere increase markedly with age across early to mid-adolescence, from very low in <10 year olds to peak around age 16-17 years.[43-46] This is likely related to adolescent development, particularly cognitive development.  Self-harm is highly prevalent in young people with GID, similar to rates in young people with a range of serious mental health problems.[34]  Thus our sample is a group in whom self-harm begins at levels higher than the general population, but who will also suffer from the normative increase in self-harm across the study period.  We hypothesise no change in self-harm across the study. This is consistent with a reduction in the propensity to self-harm due to treatment at a time when there is a developmental rise in self-harm. | We will assess change by change in self-harm/suicide items score. This score combines all categories of self-harm and suicidal ideation, including intermediate and high categories of risk. This will be formally tested. |
| 4. Teacher Report Form | The Teacher Report Form (TRF) is the third element of the Achenbach ASEBA system, asking teachers similar questions to the CBCL (parents) and YSR (young person self-report). Attempts to obtain TRF data on participants were rarely successful as this relied on families organising completion and return of questionnaires. Sample size for the TRF are insufficient to report, therefore data are not available on this outcome. |  |  | Not assessed. |

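### The YSR z-score is added to remove the normal rise in distress with age, yet its 'no change' hypothesis rests on treatment offsetting that rise, which would make z fall

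*SAP*

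**What the plan says.** All of this is in the SAP, section Outcomes, domain D of the table, unless stated otherwise.

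- **D.1 (CBCL and YSR), the trend.** "Normative data show an increase in CBCL internalizing scores (i.e. psychological distress) with age in early adolescence". From this the SAP argues that a benefit would show as a smaller rise, "meaning that there will be no discernible change in psychological function over time in our cohort". It hypothesises unchanged t-scores and adds: "This is consistent with a potential reduction in distress due to treatment at a time when there is a developmental rise in distress".
- **D.1, the scale.** "Raw scores are converted for analysis to t-scores based upon broad age-ranges". The bands are not given.
- **D.2 (YSR).** The broad bands are named again as a limit of the t-score. The remedy is a z-score for age and sex: "To account for normative change across our age-range, we will also use international reference data". The entry states that YSR total problems scores rise between ages 11 and 16 in healthy young people. Referring back to the reasoning above it, it then lists unchanged t-scores and also "no change in z-scores for total problems".
- **D.2, assessment.** "Change in total problems t-score will be tested". The z-score change is to be estimated with a mean and 95% CI, without a test.
- **C.1 (bone mineral density).** Absolute BMD is expected to stay level. The BMD z-score is expected to fall, because the age norm rises while the patient's value does not.
- **Analysis methods.** Formal tests are paired before/after t-tests. No equivalence margin is stated, and the small sample is given as the reason for simple methods.

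**The concern.** The D.1 argument needs a scale on which the normal age trend is still visible. Only there can a treatment that cancels the trend appear as a flat line. The YSR z-score is built so that the trend is no longer visible. Carrying the flat-line prediction over to it means that the stated hypothesis is the result expected if treatment does nothing relative to peers, while the stated rationale predicts a fall.

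What is at stake is the reading of a null YSR result. Of the two YSR scores, z is better able to set the cohort's course against the normal course, but it carries a hypothesis that conflicts with its own rationale and is not tested. The tested score retains part of the age trend. A non-significant paired test on that score would match the hypothesis whether treatment offset a rise, had no effect, or the sample was too small to tell.

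**Working it through.** The SAP gives no effect size, normative slope or band limits here, so there is no plan figure to reproduce. The check is algebra with assumed values.

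**Inputs**
- Direction of the norm: rising (SAP, D.1 and D.2).
- Interval: 1 year (D.1 times the follow-up at around 12 months).
- Assumed: the norm rises linearly by s = 0.02 to 0.15 within-age SD per year; t-score bands are 7 years wide.

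**Formulas** (raw scores in within-age SD units)
- Change in z = raw change - norm change.
- Band SD = sqrt(1 + s² × 7²/12).
- Change in t within one band = 10 × raw change / band SD, because the conversion is fixed inside a band.
- Change in t when a boundary is crossed = 10 × (raw change - 7s) / band SD.

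**Scenarios.** No effect: raw change = s. Full offset: raw change = 0.

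Example, s = 0.10: band SD = sqrt(1 + 0.01 × 49/12) = 1.020. With no effect, z changes by 0.10 - 0.10 = 0 and t within a band by 10 × 0.10/1.020 = +0.98. With full offset, z changes by 0 - 0.10 = -0.10 and t within a band by 0.

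| s (SD/year) | z: no effect | z: full offset | t within band: no effect | t within band: full offset | t crossing: no effect | t crossing: full offset |
|---|---|---|---|---|---|---|
| 0.02 | 0 | -0.02 | +0.20 | 0 | -1.20 | -1.40 |
| 0.05 | 0 | -0.05 | +0.50 | 0 | -2.98 | -3.48 |
| 0.10 | 0 | -0.10 | +0.98 | 0 | -5.88 | -6.86 |
| 0.15 | 0 | -0.15 | +1.44 | 0 | -8.61 | -10.05 |

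**Reading the table**
1. On z, an unchanged score is the no-effect result. A partial offset of a fraction f gives raw change (1 - f)s, so z changes by (1 - f)s - s = -fs. Any offset predicts a fall.
2. On t within one band, an unchanged score is the full-offset result. The D.1 argument is therefore coherent there. For a participant who stays in one band, unchanged t and unchanged z cannot both hold exactly while norms rise.
3. This incompatibility does not extend automatically to group means. If every participant tracks the norm and a proportion p crosses a boundary, the mean t change is 10s(1 - 7p)/band SD, which is zero at p = 1/7. Without the bands, an unchanged mean t cannot be interpreted.
4. C.1 is the same algebra: a level absolute value minus a rising norm gives a falling z. D.2 predicts the opposite without explanation.

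**The case against.** The strongest reply is that the benefit sentence is attached to t-scores only, and that broad-band t-scores do not fully remove the age trend. This stands. A reader might infer that age standardisation removes the rise from every score in D.1 and D.2, so that the D.1 argument fails outright. The SAP does not support that: within a band the conversion is fixed, and a flat t-score can reflect an offset. The rationale reaches the z-score only through the cross-reference in D.2.

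A reader might also extend the point to self-harm (D.3), where a flat score carries the remark "This is consistent with a reduction in the propensity to self-harm due to treatment". That score is an unstandardised sum of two items, so the standardisation argument does not reach it. Only the general caveat applies: without a control group, a flat score cannot separate benefit from no effect.

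A third tempting inference is that the sponsor will report any null as benefit. The wording says only that a flat result is consistent with a potential reduction, and no analysis rule counts a null as benefit.

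It can also be said that the z-score will be reported with its CI, so that which score gets the p-value is partly preference, and that shifts of the assumed size may not be discernible in a small sample. Both are fair. They reduce the weight of the testing point but do not repair the hypothesis.

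Finally, a fall in z would not by itself show benefit. D.1 says that the cohort starts above population distress levels, and in an uncontrolled before/after comparison regression to the mean could also lower z.

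**Conclusion.** The inconsistency is real and confined to the YSR total problems z-score hypothesis in D.2. Given the rising norms that the SAP itself states, an offset predicts a fall in z and an unchanged z means that the cohort followed the reference population. The direction needs no assumed figure. The size does: for an assumed slope of 0.02 to 0.15 SD per year over one year, the two readings differ by 0.02 to 0.15 SD, which is the whole of a full offset.

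For the t-scores the conclusion is weaker. The offset reading is possible within a band, but a non-significant paired test with no equivalence margin and undisclosed bands cannot distinguish it from no effect.

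**What to change.** 1. **D.2, hypothesis.** Restate it so that an offset of the normative rise predicts a fall in z, and an unchanged z means no departure from the reference course. Add that a fall in this uncontrolled cohort could also reflect regression to the mean.
2. **D.2, assessment.** Make the change in YSR total problems z-score the tested YSR outcome, with the t-score descriptive. At the least, base any interpretation relative to norms on the z-score and its 95% CI. State the t-score age bands in either case.
3. **D.1.** Qualify the benefit sentence: a non-significant before/after change in t-score cannot separate an offset from no effect.
4. **D.3.** Add only the caveat that a flat, uncontrolled score cannot separate benefit from no effect.

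The cost is SAP wording. The z-score is already planned, so no new data are needed. If z becomes the tested outcome, the sponsor should also say whether the predictor regressions in Analysis methods, which use the YSR total t-score, stay on that scale. The downside for the sponsor is that flat results can no longer be presented as suggestive of benefit.
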